**Methods/design:**

90 patients aged between 16 to 60 years, who meet the diagnostic criteria for CFS and have been diagnosed by their medical practitioner, will be randomly recruited into groups consisting of Intermittent exercise, Graded exercise and usual care (Control). The outcomes will be measured pre-study (Week 0) and post-study (Week 13). Primary outcomes are VO_2peak_, anaerobic threshold, peak power, levels of fatigue, immune cell (CD3^+^CD4^+^, CD3^+^CD8^+^, CD19^+^, CD 16^+^CD56^+^) concentrations and activation. Secondary outcomes include onset of secondary CFS symptoms (e.g. fever, swollen lymph nodes), wellness, mood and sleep patterns. Primary analysis will be based on intention to treat using logistic regression models to compare treatments. Quantitative data will be analysed using repeated measures ANOVA with a linear model, and Cohen’s effect size. Qualitative data such as participants’ responses (e.g. changes in mood and other reactions) following the exercise modalities will be read and sections demarcated. A code will be applied to each segment. A prevalence of codes will be considered thematically.

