## Methods

### Design

This study is a randomised controlled trial that will compare the outcomes of a 12-week intermittent cycling exercise program to a graded exercise cycling program and standard care (rest and lifestyle advice). The primary outcomes of the study are aerobic capacity (VO_2peak_), perceived exertion, fatigue, muscle pain, immune cell counts, lymphocyte (CD4^+^, CD8^+^, CD19^+^, CD16^+^56^+^) concentrations and function. Secondary outcomes are wellness indices and physiological adaptations to exercise (changes in heart rate, heart rate variability, blood pressure, body composition, anaerobic threshold) and measures of presence, severity and type of fatigue (mental and physical). Southern Cross University Research Ethics Committee has approved all study procedures (HREC ECN-13-066).

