### Outcome measures

All outcome measures will be collected at baseline (Week 0) and after the exercise interventions (Week 13). Trained research personnel blinded to the randomization procedures will conduct the initial participant screenings and baseline assessments, which include a full medical history, resting heart rate, resting blood pressure and anthropometry (height; weight; BMI; waist, hip and limb girths), fatigue severity and wellness questionnaires. The project outcome measures consist of a full cell count; lymphocyte receptor flow cytometric assays; incremental cycling test (VO_2peak,_ anaerobic threshold); spirometry; Personal Well Being Index [33] and Fatigue Severity Scale [34].

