#### Fatigue and muscle pain

RPE and fatigue will be recorded at rest and during the incremental exercise test. Participants will be asked to complete a linear pain scale (0 – 10) to indicate if they have any muscle or joint stiffness or soreness prior to the exercise test, immediately post-exercise and also 24 hours post-exercise test. RPE and pain scales will also be completed at every training session to carefully monitor symptoms. The Fatigue Severity Scale [34] and the Chalder Fatigue Scale [39], both CFS-specific, will be administered pre- and post-study to assess the severity and nature of the fatigue, mental and physical.

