### Statistical analyses

Primary analysis will be via intention-to-treat with all patients included regardless of dropout or level of adherence. Missing data will be imputed according to the maximum likelihood expectation algorithm via the Statistical Package for the Social Sciences (SPSS© Version 19.0). Physiological and exercise test data will be presented as the mean ± standard deviation, with confidence intervals used to express group differences. Changes between groups and the time effect for each group will be determined by repeated measures analysis of variance with a Bonferroni adjustment for significant differences between groups. Cohen’s Effect sizes and 90% confidence intervals will be calculated, to utilise a magnitude-based approach to inferences [41], with the following descriptors applied: (1) Effect size thresholds: <0.2 trivial, <0.6 small, <1.2 moderate, <2.0 large, <4.0 very large, >4.0 extremely large, and (2) Thresholds for assigning qualitative terms to chances of substantial effects: <0.5%, almost certainly not; <5.0%, very unlikely; <25%, unlikely; <75%, possible; >75%, likely; >95%, very likely; >99.5%, almost certain. An effect is unclear if its confidence interval includes both substantial increases and decreases [41]. A p value of < 0.05 will be considered indicative of statistical significance; clinical significance will be interpreted in light of the meaningfulness and magnitude of the adaptations observed. Data from linear pain scales will be recorded pre- and post-study, and reported as frequencies of scores between 0 and 10. Data will then be analysed using ANOVA (group and time effects). Data from wellness indices will be recorded pre and post, combined into domains and a representative total score from the time points analysed using an ANOVA. Data (non parametric) from the Fatigue scales, also measured at time points, will be collated and analysed using a Kruskall-Wallis test.

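### The fatigue scales are measured twice but assigned a Kruskal-Wallis test with no stated response value; a baseline-adjusted comparison should replace it

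*Protocol article*

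**What the plan says.** Protocol article, Statistical analyses: data "from the Fatigue scales, also measured at time points, will be collated and analysed using a Kruskall-Wallis test". The sentence calls these data non-parametric. It does not say whether the value tested is the Week 13 score, the change, or both scores together.

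Earlier in the same section, changes between groups and the time effect are to be assessed by "repeated measures analysis of variance with a Bonferroni adjustment for significant differences between groups". Pain scores get an ANOVA with group and time effects.

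Timing, from Fatigue and muscle pain: the two scales "will be administered pre- and post-study to assess the severity and nature of the fatigue, mental and physical". From Outcome measures: "All outcome measures will be collected at baseline (Week 0) and after the exercise interventions (Week 13").

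Status of fatigue:
- The abstract's Methods/design lists "anaerobic threshold, peak power, levels of fatigue" among the primary outcomes.
- Design lists "perceived exertion, fatigue, muscle pain, immune cell counts" among the primary outcomes.
- Design then puts "measures of presence, severity and type of fatigue (mental and physical") among the secondary outcomes. That closely matches the description of the two scales under Fatigue and muscle pain.

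**The concern.** Kruskal-Wallis compares independent groups on a single value per person. Here each person supplies two values, and the question is whether fatigue at Week 13, or its change, differs between arms. A test with no place for time or for a covariate fits that question only after the two scores have been reduced to one, and the article does not say how. Two analysts could follow the sentence and obtain different p-values.

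Fatigue is part of the stated primary aim (exercise against standard care), and hypothesis 2 expects less of it with intermittent than with graded exercise. What is at stake is the validity of the fatigue result under one reading, and avoidable loss of precision under the others.

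**Working it through.** **Inputs from the article.** Three arms, 25 evaluable per arm and alpha 0.05 (Sample size and power calculation); two measurements per participant (Outcome measures; Fatigue and muscle pain).

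**Assumptions.** Pre-post correlation r = 0.3 to 0.8; bivariate normal scores with SD 1; both exercise arms shifted by 0.6 SD and control unchanged. The article gives none of these.

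**The plan's own figure.** The only stated power, 82% with 25 per group, is for VO2peak. It cannot be reproduced because no effect size, SD or correlation is given. Solved backwards as a one-way ANOVA it implies f = 0.375, that is 0.80 SD for each exercise arm against control. No power is stated for fatigue.

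**Reading A: both time points pooled by group.** Two correlated ranks per person are treated as independent, so the null test statistic is inflated by about (1 + r_s), where r_s = (6/π)·arcsin(r/2) is the rank correlation. On 2 degrees of freedom the true error is about 0.05^(1/(1 + r_s)).

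| r | r_s | formula | simulated |
|---|---|---|---|
| 0.3 | 0.288 | 9.8% | 9.9% |
| 0.5 | 0.483 | 13.3% | 13.2% |
| 0.7 | 0.683 | 16.9% | 16.6% |
| 0.8 | 0.786 | 18.7% | 18.6% |

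Power is also poor, about 34–39%, because half of the observations predate treatment. A variant that tests the six group-by-time cells rejects about 61% of the time when all arms merely improve equally by 0.5 SD, so it is not a group comparison.

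**Reading B: Week 13 only. Reading C: change scores.** Both keep type I error at about 5%. On the normal scale, the variance of each person's contribution to a group contrast is:
- Week 13: 1
- change: 2(1 − r)
- ANCOVA: 1 − r²

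| r | Week 13 | change | ANCOVA |
|---|---|---|---|
| 0.3 | 1 | 1.40 | 0.91 |
| 0.5 | 1 | 1.00 | 0.75 |
| 0.7 | 1 | 0.60 | 0.51 |
| 0.8 | 1 | 0.40 | 0.36 |

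ANCOVA has the smallest variance in every row. Change is worse than Week 13 alone at 0.3 and equal to it at 0.5. This ordering holds for any between-group contrast, including intermittent versus graded exercise.

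Simulated power at 0.6 SD (separate runs agree to about 2 points):

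| r | Kruskal-Wallis, Week 13 | Kruskal-Wallis, change | ANCOVA | rank ANCOVA |
|---|---|---|---|---|
| 0.3 | 53% | 38% | 59% | 58% |
| 0.5 | 53% | 54% | 70% | 66% |
| 0.7 | 53% | 76% | 85% | 81% |
| 0.8 | 53% | 92% | 95% | 93% |

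Loss against ANCOVA, in points:
- Week 13: 59 − 53 = 6; 70 − 53 = 17; 85 − 53 = 32; 95 − 53 = 42.
- Change: 59 − 38 = 21; 70 − 54 = 16; 85 − 76 = 9; 95 − 92 = 3.

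At the 0.80 SD implied by the VO2peak calculation, for r = 0.3 / 0.5 / 0.7, the pattern is the same: Week 13 about 79% throughout, change 64 / 79 / 95%, ANCOVA 84 / 91 / 98%.

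**The case against.** A reader might infer that the stated test must produce either an inflated error rate or much lower power. The article does not support that.

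- **Change scores are a natural reading.** The text neither states nor excludes it. It gives one independent value per person, keeps 5% error, uses the baseline and addresses group-by-time. At 0.80 SD it loses only 1 to 3 points against the repeated measures ANOVA planned for other outcomes (64 / 79 / 95% against 67 / 82 / 96%). Most of its shortfall against ANCOVA comes from using change rather than covariate adjustment, not from ranking. This stands.
- **Pooling is the least likely reading.** *Collated* ordinarily means assembled, and nothing says that the scores are stacked as independent observations. The 10–19% is therefore conditional, not a stated error.
- **The size rests on an unstated correlation.** The Week 13 loss is about 6 points at r = 0.3. Normal data also favour ANCOVA. Against rank ANCOVA, the change-score loss is smaller: about 20, 12, 5 and 1 points. This stands.
- **The power figures do not test hypothesis 2.** That hypothesis compares intermittent with graded exercise, and both arms were shifted equally. The figures bear on exercise against usual care, as in the primary aim. Only the variance ordering carries over.
- **Primary status is not secure.** A reader might take it as settled that these scales are primary. Design supports both placings, and fatigue is also recorded during the exercise test and at training sessions.
- **An article condenses.** Which score is analysed may be set out in a fuller document. That disposes of a complaint about missing detail alone. It does not dispose of the choice of test, which the article does make and which cannot take the baseline as a covariate.

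**Conclusion.** The point holds in limited form. The article assigns to two-occasion fatigue scores a test that takes one value per participant and cannot adjust for baseline or model group-by-time, and it leaves the value tested open. Under one reading the p-values would be invalid (type I error about 10–19%). Under the two valid readings the cost against ANCOVA is about 6 to 42 points of power (Week 13) or 3 to 21 points (change). These sizes rest on 25 per arm, normal scores, an assumed 0.6 SD shift in both exercise arms and r between 0.3 and 0.8.

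This should be fixed because a better analysis of data already collected is available. It is not a flaw that invalidates the fatigue analysis whichever way the sentence is read. Whether it touches a primary outcome cannot be decided until the article's two placings of fatigue are reconciled.

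**What to change.** In Statistical analyses, replace the Kruskal-Wallis sentence. For each scale, compare the Week 13 total between the three groups with the Week 0 total as covariate. Rank ANCOVA suits the plan's view of the scores as non-parametric; ANCOVA or an ordinal model is also acceptable, provided that one is named in advance. Add Bonferroni-adjusted pairwise contrasts, including intermittent versus graded exercise, so that hypothesis 2 is tested directly.

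If Kruskal-Wallis is kept, the least that is needed is a statement that it is applied to each participant's change score. That secures validity but not the precision gained by adjustment.

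In Design and the abstract, state whether the Fatigue Severity Scale and the Chalder Fatigue Scale are primary or secondary, and which measurement the primary outcome called fatigue refers to.

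The cost is wording only: no new data, visits or participants.

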## Discussion

The results of this study will contribute evidence to best-practice for management of CFS. Findings from this research could improve health outcomes by reducing fatigue, increasing aerobic capacity, wellness and immune responses. Desired research outcomes could also be applied to the management of other chronic health conditions where fatigue is a contributing factor.
